### Provisions for posttrial care {30}

Trial outcomes will be collected until primary hospital discharge after birth or 28 days after estimated delivery date (EDD), whichever is sooner. IMP will be stopped at the end of pregnancy, so any postnatal data is unlikely to reflect the effect of the intervention. Postnatal care will be determined by the woman’s usual care team. Serious adverse event (SAE) data on maternal and neonatal death will be collected up to 28 days after discharge if the research team become aware of any such events.

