### Outcomes {12}

The following outcomes are collected from randomisation to maternal and neonatal hospital discharge or up to 28 days after EDD, whichever is sooner.

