**Fig. 1 Fig1:**
[figure not shown]
Participant flow through CaPE trial

**Table 1 Tab1:** Schedule of assessments

				From randomisation		
Visit	Screening	Baseline	After recruitment — as identified	Every 4 weeks until delivery	Admission for delivery	Hospital discharge/estimated delivery date plus 4 weeks
Eligibility check	x	x				
Dietary calcium intake survey		x				
Intention to take or taking vitamin D		x				
Intention to take or taking aspirin		x				
Valid informed consent		x				
Randomisation		x				
Dispensing of IMP		x				
Adherence text message (automated)				x		
Outcome CRF Completion						x
Serious adverse events (SAE)			x			x *
Return unused IMP (pill counting)					x**	

*Any events meeting the trial definition of a reportable SAE should be reported to the CaPE trial office within 24 h of the site becoming aware. SAE reporting begins from the commencement of trial treatment and ends at hospital discharge after birth, 28 days after EDD, death, and complete withdrawal or lost to follow-up, whichever occurs sooner. The only caveat to this is in regard to death of the participant or neonate — this must be reported up to hospital discharge following birth or up to 28 days after EDD, whichever occurs later. Should a participant completely withdraw or be lost to follow-up, the requirement to report death will halt on that date

**At point of admission for delivery or as close to as possible

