### Interim analyses {21b}

Interim analyses of safety and efficacy for presentation to the independent Data Monitoring Committee (DMC) will take place during the trial. The committee has agreed on the manner and timing of such analyses and includes the analysis of the primary and major secondary outcomes, the primary outcome event rate, and full assessment of safety (SAEs) at least at annual intervals. Criteria for stopping or modifying the trial based on this information will be ratified by the DMC. Details of the agreed plan are written into the SAP and DMC charter.

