### Adverse event reporting and harms {22}

CaPE sites will be required to report any adverse events (AEs) throughout their participation in the trial, from the day of commencement of trial treatment until primary hospital discharge after birth or 28 days after EDD, whichever is sooner. The only caveat to this is death of the participant or neonate — this must be reported up to hospital discharge following birth or up to 28 days after EDD, whichever occurs later. The recording and reporting of AEs will be in accordance with the UK Policy Framework for Health and Social Care Research, the Principles of GCP as set out in the UK Statutory Instrument (2004/1031 and subsequent amendments), and the requirements of the Health Research Authority (HRA) and The Medicines for Human Use (Clinical Trials) Regulations 2004 and amendments thereof.

AEs are rarely encountered in participants taking additional dietary calcium, and previous trials in pregnant women have consistently shown no increase in AEs. As the safety profile of the IMP used in this trial is well characterised and mild side effects have significant overlap with pregnancy symptoms (nausea, dyspepsia, abdominal pain, itching, etc.), we will only be reporting AEs that have a higher probability of being related to calcium intake on the outcome CRF. These include the following:

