### Reportable adverse events

New diagnosis of maternal hypercalcaemiaNew diagnosis of renal stones in the woman (confirmed on imaging, after starting of IMP)Milk alkali syndrome (hypercalcaemia, alkalosis, and biochemical evidence of renal impairment)Neonatal hypocalcaemia requiring treatmentSymptomatic neonatal hypocalcaemia (usually presenting as neonatal seizures)

Reportable adverse events will be recorded in the study database, and the assessment of severity, seriousness, and relatedness to the IMP (causality) will be documented.

An AE that meets the definition of serious (i.e. results in death, is life-threatening, requires hospitalisation or prolongation of existing hospitalisation, results in persistent or significant disability or incapacity, is a congenital anomaly/birth defect, is otherwise considered medically significant by the investigator) will be reported as an SAE. SAEs will be recorded on the SAE CRF and must be signed off by the site PI and CI. The PI will also report the SAE to their own trust in accordance with local practice and to the trial office. All SAEs are reviewed by the DMC during the DMC meetings throughout the trial.

However, there are SAEs that are considered expected for the trial population. These are recorded in the case note review but are not considered to be critical to evaluations of the safety of the trial and do not need to be reported. These include the following:

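### The reason given for stopping collection at discharge does not fit neonatal hypocalcaemia, and a non-fatal case first seen after discharge has no required route to the DMC

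*Protocol article*

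**What the plan says.** **Window and reason.** Provisions for posttrial care {30} closes outcome collection at the earlier of primary discharge after birth and EDD plus 28 days, and explains: "IMP will be stopped at the end of pregnancy, so any postnatal data is unlikely to reflect the effect of the intervention". Outcomes {12} sets the same kind of window: "The following outcomes are collected from randomisation to maternal and neonatal hospital discharge or up to 28 days after EDD, whichever is sooner".

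**Harms selected for reporting.** Adverse event reporting and harms {22} narrows reporting on purpose: "we will only be reporting AEs that have a higher probability of being related to calcium intake on the outcome CRF". The list under Reportable adverse events includes neonatal hypocalcaemia twice, once as treated and once as symptomatic, with seizures named as the usual presentation. The treated form is also a secondary outcome for the baby, labelled an adverse effect.

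**Exception.** Section {22} closes adverse event reporting at the same cut-off and adds "The only caveat to this is death of the participant or neonate". The Table 1 footnote does the same for serious adverse events (SAEs): "The only caveat to this is in regard to death of the participant or neonate". Sections {30} and {20a} also make an exception only for maternal and neonatal death.

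**Oversight.** Reportable adverse events states "All SAEs are reviewed by the DMC during the DMC meetings throughout the trial". Interim analyses {21b} gives the DMC a "full assessment of safety (SAEs) at least at annual intervals".

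**The concern.** The sentence in {30} sets aside all postnatal data because exposure has ended. Neonatal hypocalcaemia follows exposure in pregnancy but can only be observed after birth. The sponsor chose to list it because it is more likely than other events to be related to calcium, so the stated reason and the harm list pull in opposite directions on this event.

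The practical consequence lies in the reporting rules. A baby who goes home and is readmitted with hypocalcaemic seizures falls outside the window, and the only exception does not apply. At stake is safety oversight of one named, potentially serious neonatal event. Estimation of the treatment effect is not at stake.

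**Working it through.** The plan gives no figure on this point, so there is none to reproduce. The check has two parts.

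**Part 1: follow one case through the rules.** Take a baby discharged well, then readmitted with hypocalcaemic seizures who survives.

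1. Is it a listed event? Yes: the symptomatic form is under Reportable adverse events.
2. Is it serious? Yes: the definition there includes an event that "requires hospitalisation or prolongation of existing hospitalisation".
3. Is it exempt as expected? No: Expected neonatal serious adverse events names only admissions for sepsis and for prematurity.
4. Is it inside the reporting window? No: {22} and the Table 1 footnote have closed at discharge.
5. Does the exception apply? No: it covers death only.

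Only step 4 keeps the case out. No report is required even if the site knows of the case. A baby who has not left hospital is captured up to EDD plus 28 days.

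**Part 2: size the fix.** The article gives no onset timing, length of stay or event rate for neonatal hypocalcaemia, so the number of cases missed cannot be computed. What can be sized is how many births an amendment would reach and how many reports it might bring.

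Inputs from the article:
- 7,756 women (Sample size {14})
- recruitment from 4 August 2022 to June 2025, and current version v2.0 of 8 August 2024 (Trial status)
- randomisation at 12 to 22 weeks (Trial design {8})

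Assumptions:
- even accrual, ending 30 June 2025
- birth at 40 weeks (earlier births lower the coverage)
- one baby per woman
- 1 to 10 post-discharge cases per 10,000 babies, all of them noticed

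Days:
- recruitment: 4 August 2022 to 30 June 2025 = 1,061
- 8 August 2024 to 30 June 2025 = 326
- randomisation to birth: (40 − 22) × 7 = 126, up to (40 − 12) × 7 = 196

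Coverage = (recruitment days left + days from randomisation to birth) / 1,061.

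- In force on 8 August 2024: (326 + 126)/1,061 = 42.6% and (326 + 196)/1,061 = 49.2%, or 3,304 to 3,816 of 7,756 women. This is a ceiling that cannot be reached, because v2.0 of that date is already the current version and any further amendment comes later.
- In force on 30 June 2025: 126/1,061 = 11.9% and 196/1,061 = 18.5%, or 921 to 1,433 women.

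Reports = women covered × assumed rate.

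- End of recruitment: 921 × 1/10,000 = 0.09, up to 1,433 × 10/10,000 = 1.4.
- Ceiling: 3,304 × 1/10,000 = 0.3, up to 3,816 × 10/10,000 = 3.8.

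**The case against.** The best defence is that the sentence in {30} is a hedged rationale and does not govern what the trial collects. The trial does collect postnatal neonatal data, including treated hypocalcaemia and seizures, up to discharge. One fixed window applied alike to both blinded arms is a reasonable choice for a pragmatic trial. Section {22} adds that earlier trials in pregnancy showed no increase in adverse events. All of this stands, and it argues for a light remedy. It does not remove the mismatch between the rationale and the harm list.

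A second objection also stands. The gap matters only if hypocalcaemia first appears after discharge, and nothing in the article shows how often that happens. The remedy would yield a partial listing that depends on the site, with no rate and no valid comparison of arms.

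Two stronger readings are tempting, and neither is supported.

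- A reader might infer that such a case is shut out from the DMC, or that the promise to review every SAE is broken. The rules end a duty to report and do not forbid a voluntary report. Procedure for unblinding {17b} sets no time limit on unblinding serious, unexpected, related cases for regulators, although it creates no duty to report after discharge. The DMC may hold extra meetings for safety. Review of all SAEs most naturally means those reported. The full protocol and DMC charter are not shown.
- A reader might infer that the comparison of hypocalcaemia between arms is biased. The outcome is consistently defined as up to discharge, the window is the same in both arms, and the article contains no evidence of a differential loss.

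**Conclusion.** The point holds as a minor one about safety reporting. The reason in {30} is worded too broadly, because the article itself names a calcium-related harm that can only be seen after birth. Under the reporting rules in the article, a non-fatal case first presenting after discharge has no required route to the DMC, even when it is serious and known to the site.

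The number of such cases is unknown. No bias is shown, and neither the primary outcome nor the main inference is affected. The calculated range of 0.1 to 1.4 reports describes the yield of an amendment in force at the planned end of recruitment. It rests on the assumed rate, even accrual, birth at 40 weeks, one baby per woman and complete notice of cases. It is not an estimate of cases lost.

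**What to change.** 1. Reword the sentence in {30} so that it does not cover neonatal hypocalcaemia.
2. In {30}, {20a}, {22} and the Table 1 footnote, extend the exception for death to treated or symptomatic neonatal hypocalcaemia that the research team becomes aware of, up to 28 days after birth or the current cut-off, whichever is later. Use it for SAE reporting and DMC review only. The article already uses a birth-to-28-days period for neonatal death. State the new window in the same terms in all four places, since the death window itself is currently described in two ways: {30} and {20a} run it to 28 days after discharge, while {22} and the footnote run it to the later of discharge and EDD plus 28 days.
3. Leave the up-to-discharge outcome unchanged. List later cases separately by arm as a minimum count, not as a 28-day risk, and state which births the listing covers.

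**Cost.** The change needs a wording and SAE-form amendment with the approvals described in {25}, plus a handful of reports at most under the stated assumptions. It needs no new visit and no second case-note review. Consent under {26b} already gives access to the baby's records; whether that reaches past discharge is for the ethics committee to confirm.

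**Downsides.** Capture is passive, incomplete and may vary by site. Only births after the amendment are covered: below 43–49%, and about 12–18% if it takes force at the planned end of recruitment.

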### Outcomes {12}

The following outcomes are collected from randomisation to maternal and neonatal hospital discharge or up to 28 days after EDD, whichever is sooner.

#### Primary outcome

The primary outcome of the CaPE trial is a clinician diagnosis of pre-eclampsia, based on the International Society for the Study of Hypertension in Pregnancy (ISSHP) definition: a blood pressure ≥ 140/90 mmHg (at least two readings several hours apart) and either.Significant proteinuria (protein/creatinine ratio (PCR) of 30 mg/mmol or more) ORMaternal multiorgan dysfunction as follows:Acute kidney injury (AKI) (creatinine ≥ 90 μmol/L)Liver involvement (elevated transaminases, e.g. alanine transaminase (ALT), or aspartate transaminase (AST) > 40 IU/L) with or without right upper quadrant or epigastric abdominal pain).Neurological complications (including eclampsia, altered mental status, blindness, stroke, clonus, severe headaches, persistent visual scotomata)Haematological complications (thrombocytopenia — platelet count below 150,000/μL, DIC, haemolysis).ORUteroplacental insufficiency (foetal growth restriction, abnormal umbilical artery Doppler, stillbirth) developing at or after 20-week gestation

#### Key secondary outcomes

The following are considered key secondary outcomes for the analysis as they are clinically very important and have a potential to be impacted by calcium based on data from previous trials as follows:Severe pre-eclampsia index: any one of severe pre-eclampsia, early onset pre-eclampsia < 32 weeks, eclampsia, placental abruption, HELLP, or severe gestational hypertension [28]Preterm birth < 37 weeks

#### Other secondary outcomes

##### For the woman

Pre-eclampsia Core Outcome Set (COS) outcomes, namely:DeathEclampsiaStrokeVisual impairment: retinal detachment or cortical blindnessPulmonary oedemaAcute kidney injury: creatinine ≥ 90 μmol/LLiver capsule haematoma or rupture (confirmed on ultrasound)Raised liver enzymes: ALT or AST > 40 IU/LLow platelets < 150,000/μLAbruptionPostpartum haemorrhage: estimated or measured blood loss ≥ 500 mL and ≥ 1000 mL after birthAdmission to intensive therapy unit (ITU)oAny admissionoDays of admissionUse of mechanical ventilation (for other than caesarean section)

In addition to these COS outcomes as follows:Gestational hypertension: new onset hypertension ≥ 140/90 mm Hg (at least two measurements several hours apart) after 20-week gestation in the absence of proteinuria or other features of pre-eclampsiaSevere hypertension: blood pressure ≥ 160 systolic and/or 110 mm Hg diastolicSevere gestational hypertension: new onset hypertension ≥ 160 mm Hg systolic and/or 110 mm Hg diastolic after 20-week gestation in the absence of proteinuria or other features of pre-eclampsiaSevere pre-eclampsia, defined as pre-eclampsia with severe features (American College of Obstetricians and Gynecologists definition) including severe hypertension or low platelets < 100,000/μL, abnormal liver function tests (liver enzymes at least twice the upper limit of normal) and right upper quadrant pain not accounted for by other diagnoses, abnormal renal function (creatinine > 1.1 mg/dL), pulmonary oedema, visual impairment, severe headache unresponsive to medication, and no other cause found.HELLP syndrome based on a clinician’s diagnosis, supported by low platelets and raised liver enzymes as defined above with or without evidence of haemolysis (raised lactate dehydrogenase enzyme or blood film)Early onset pre-eclampsia < 32 weeksPre-eclampsia requiring delivery before 37 weeksUse of magnesium sulphate for pre-eclampsiaOnset of birth: spontaneous, induction of labour, or caesarean sectionMode of birth: spontaneous vaginal birth, assisted vaginal birth, elective pre-labour caesarean section, emergency pre-labour caesarean section, and emergency caesarean section in labourAdverse effect: new diagnosis of maternal hypercalcaemiaAdverse effect: renal stones (confirmed on imaging, after starting IMP)Adverse effect: stopping of medication due to adverse effects.

##### For the baby

COS outcomes, namely:Any death in the baby up to hospital discharge. Data will be collected separately for the following:oFetal loss < 24-week gestation (miscarriage)oFetal loss ≥ 24-week gestation (stillbirth)oNeonatal death (from birth up to 28 days)Early neonatal death (up to 7 days after birth)Late neonatal death (from 7 days to 28 days)oPerinatal death: stillbirth or neonatal death up to 7 daysoTermination of pregnancyGestational age at delivery (median, < 28 weeks, < 32 weeks, < 37 weeks)Birthweight (mean, < 3rd centile, < 10th centile)Admission to neonatal unit (NNU)oAny admissionoLevel of neonatal careoDays of admissionRespiratory support morbidityoUse of surfactantoUse of mechanical ventilationoUse of noninvasive ventilationoUse of supplementary oxygenoDuration of respiratory supportNeonatal seizuresNeonatal brain injury as follows:oHypoxic ischaemic encephalopathy requiring therapeutic hypothermiaoNeonatal strokeoSevere intraventricular haemorrhage (IVH) grade III/IV and/or cystic periventricular leukomalacia

In addition to these COS outcomes as follows:Chronic lung disease (CLD) requiring oxygen therapy at 36-week post-menstrual ageNecrotising enterocolitis (NEC) requiring surgeryRetinopathy of prematurity (ROP) requiring treatment with laser or anti-VEGF injectionComposite of death or serious morbidity: Death or CLD, IVH grade III/IV, NEC requiring surgery, or ROP requiring treatmentAdverse effects: Neonatal hypocalcaemia requiring treatment

Whilst the outcomes listed above will allow us to capture all events relevant to the trial’s main question on prevention of pre-eclampsia, we will seek consent from trial participants to be approached for long-term data linkage studies in the future (requiring additional and separate funding and ethical approval). This could include assessment of cardiovascular health for both women and babies.

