### Data collection and management

#### Plans for assessment and collection of outcomes {18a}

A summary of the data being collected is provided in Table 1. Prior to opening to recruitment, each site participating in CaPE will receive training on the protocol and data collection procedures during the site initiation visit. Once an eligible participant has provided informed consent, baseline data (including intention to take vitamin D, intention to take aspirin, and risk factors for pre-eclampsia) will be recorded within the randomisation data collection form by the site research team. Participants will be required to complete a short, validated dietary calcium intake questionnaire [32] immediately after randomisation, and their daily baseline dietary calcium intake will be calculated via a web-based calculator [33] and recorded. Participants will remain blinded to these results to avoid influencing their dietary behaviour. All outcome data will be captured on the electronic case report forms (CRFs) available through the CaPE database. This data will be collected from standard maternity notes (both electronic medical records and paper-based records), by case note review, at primary hospital discharge or 28 days after EDD, whichever is sooner. Plans for data quality and monitoring are reported in the section ‘Frequency and plans for auditing trial conduct {23}’.

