## Statistical methods

### Statistical methods for primary and secondary outcomes {20a}

The separate statistical analysis plan (SAP) provides a more comprehensive description of the planned statistical analyses. A brief outline of these analyses is given below.

The primary comparison groups will be composed of those randomised to usual care plus an additional dietary calcium supplement of 2 g per day versus those randomised to usual care plus a placebo (the randomised groups).

In the first instance, all analyses will be based on the intention to treat principle, i.e. all participants will be analysed in the treatment group to which they were randomised, irrespective of adherence or other protocol deviation. For all outcome measures, appropriate summary statistics will be presented by group (e.g. proportions/percentages, mean/standard deviation, or median/interquartile range). All outcomes will be presented with point estimates (e.g. relative risks, incident rate ratios, hazard ratios, mean differences) and 95% confidence intervals. The final analysis dataset will only include items up to and including hospital discharge of the mother and baby or 28 days after EDD (whichever occurs sooner), with the exception of SAE data on maternal and neonatal death which will be collected up to 28 days after discharge if the research team become aware of any such events. Analyses will be conducted using complete case analysis, with participants excluded from the intention-to-treat analysis if their outcome data is missing.

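### Neonatal death to 28 days is a listed outcome, but the collection rules for these deaths disagree and none runs to 28 days after birth

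*Protocol article*

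**What the plan says.** The protocol article deals with deaths of babies in several places.

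- **Outcome definition (For the baby).** The parent outcome is "Any death in the baby up to hospital discharge". Beneath it are neonatal death from birth to 28 days, early neonatal death to 7 days, and "Late neonatal death (from 7 days to 28 days".
- **General collection rule.** Outcomes {12} says outcomes are "collected from randomisation to maternal and neonatal hospital discharge or up to 28 days after EDD, whichever is sooner". Provisions for posttrial care {30} says the same: "Trial outcomes will be collected until primary hospital discharge after birth or 28 days after estimated delivery date (EDD), whichever is sooner". Plans for assessment and collection of outcomes {18a} describes collection "by case note review, at primary hospital discharge or 28 days after EDD, whichever is sooner".
- **Death reporting rule.** Adverse event reporting and harms {22} sets the same sooner cut-off for adverse events, then makes an exception: "The only caveat to this is death of the participant or neonate", of which it says "this must be reported up to hospital discharge following birth or up to 28 days after EDD, whichever occurs later". The footnote to Table 1 repeats this.
- **Analysis dataset.** Statistical methods {20a} restricts the dataset to the sooner of discharge or EDD plus 28 days. It exempts serious adverse event data on maternal and neonatal death, which are "collected up to 28 days after discharge if the research team become aware of any such events". Provisions for posttrial care {30} carries the same exception.

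**The concern.** A 28-day mortality outcome needs a 28-day observation period that is the same for every baby. Here the label promises 28 days of life, the parent outcome stops at discharge, and the collection rules are tied to discharge or the EDD, never to birth. Observation time therefore depends on length of stay and gestation at birth, both of which are determined after randomisation.

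The Secondary outcomes section of the statistical methods analyses dichotomous baby outcomes as risk ratios, which presuppose a common risk period. Preterm birth is a key secondary outcome because calcium might affect it, so gestation at birth cannot be assumed equal between arms. At stake is whether the reported neonatal and late neonatal death rates mean what their labels say, and whether two sites following the article would record the same deaths.

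**Working it through.** The protocol article gives no figure for this point. Its sample size reproduces: 3684 per arm for 11.5% against 9.2% at 90% power, so 7368 in total, and 7368 / 0.95 = 7755.8, or 7756. It does not depend on the neonatal death window.

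**Inputs.** The windows are those set out above. The EDD is taken as 40+0 weeks. The article gives no lengths of stay, so those below are assumptions for illustration.

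**Formulae (age in days at which each rule ends).**
- Age at EDD plus 28 days: E = (40 − gestation in weeks) × 7 + 28
- General rule: the smaller of stay and E
- Mandatory death rule: the larger of stay and E
- Analysis exception: stay + 28, conditional on the team learning of the death

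**Baby discharged on day 2 (assumed).**

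| Gestation at birth | E | General rule | Mandatory death rule | Analysis exception (if known) |
|---|---|---|---|---|
| 34+0 | 70 | 2 | 70 | 30 |
| 37+0 | 49 | 2 | 49 | 30 |
| 40+0 | 28 | 2 | 28 | 30 |
| 41+0 | 21 | 2 | 21 | 30 |
| 42+0 | 14 | 2 | 14 | 30 |

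**What follows for the 28-day outcome.**
- The general rule reaches day 28 only if the baby stays at least 28 days and is born by 40+0.
- The mandatory rule reaches day 28 for every baby born by 40+0. For a baby born later and discharged early, it loses one day for each day past the EDD: 28 − 21 = 7 days at 41+0 and 28 − 14 = 14 days at 42+0. Of the 21 days from day 7 to day 28, that is 7/21 = 33% and 14/21 = 67%.
- The exception always passes day 28, because stay + 28 cannot be less than 28, but it is not systematic.

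**Two cases where the rules part (assumed stays).**
- Born at 41+0, discharged on day 2, dies on day 25. This is a late neonatal death. The mandatory duty ended on day 21. The exception runs to day 30, so the death is counted only if someone happens to learn of it.
- Born at 34+0, discharged on day 14, dies on day 50. The mandatory rule runs to day 70, so the death must be reported. The exception ended on day 14 + 28 = 42, so it falls outside the analysis dataset. At day 50 it is not a neonatal death under the 28-day label, but it shows that the two death rules do not describe the same set of deaths.

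**The case against.** The strongest reply is that a general outcome window with a stated exception for death is not a contradiction. The adverse event section calls death the only caveat to the sooner cut-off, and on that reading the sooner rule does not govern deaths. This largely stands. It does not remove the difference between the two rules that do govern deaths after discharge: one is mandatory and tied to discharge or the EDD, the other is tied to discharge plus 28 days and depends on the team becoming aware.

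A second reply is that the 28-day items are only timing categories within death before discharge. That is coherent, but late neonatal death would then mean in-hospital death only. The labels do not say so, and the analysis section's provision for deaths after discharge points the other way.

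A reader might infer four stronger things, which the document does not support:
- **That the analysis dataset stops at discharge.** Statistical methods {20a} expressly exempts neonatal death data.
- **That late neonatal death cannot be measured for most babies.** A day-2 discharge leaves 26 of 28 days outside the general rule, but the mandatory death rule covers all 28 days for births by 40+0.
- **That perinatal death, which counts deaths to 7 days, is equally affected.** The mandatory rule still gives 14 days at 42+0, and (40 − 43) × 7 + 28 = 7 days even at 43+0.
- **That mortality is biased in favour of calcium.** Both arms follow the same rules under blinding. A difference needs calcium to alter gestation or stay, and deaths after discharge to be missed as a result.

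**Conclusion.** Wrong as written, for secondary outcomes only. The article defines neonatal death to 28 days of age under a parent outcome that ends at discharge, and its two rules for deaths after discharge disagree in end date and in whether collection is obligatory. Neither is anchored to birth.

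The certain consequence is uneven ascertainment of late neonatal death. Under the mandatory rule the shortfall is confined to babies born after the EDD and discharged before day 28: 7 days at 41+0 and 14 days at 42+0. This takes the EDD as 40+0 and coverage as the period in which reporting is required, which does not guarantee that every death is found. The number of deaths affected cannot be estimated, because the article gives no distribution of gestation, length of stay or deaths.

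Differential ascertainment between arms is possible but conditional on a calcium effect on gestation or stay. These outcomes are not hypothesis-tested, and the primary outcome and sample size are untouched.

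**What to change.** Adopt one death window for every baby: the later of hospital discharge or 28 days after birth. Make it the mandatory death-reporting rule in Adverse event reporting and harms {22} and the Table 1 footnote. State in Statistical methods {20a} that these deaths enter the analysis dataset without the awareness condition. Align Provisions for posttrial care {30}, Outcomes {12}, For the baby and Plans for assessment and collection of outcomes {18a}, so that the parent outcome and its 28-day categories share that period.

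If this is not feasible, drop the 28-day labels and report death before hospital discharge only.

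The cost is wording plus a small change to the site reporting rule, which lengthens the duty mainly for babies born after the EDD. For babies born before the EDD and discharged early, a birth-anchored window ends sooner than the present one (day 28 instead of day 70 in the 34+0 example). If the sponsor wants the longer period for safety, it can be kept separately and labelled as such. A new active day-28 check for the babies of about 7756 women would be a larger undertaking. Recruitment began in August 2022, so babies already past the window could be brought into line only by going back to their notes.
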